**Fig. 3 Fig3:**
[figure not shown]
Flowchart for the primary survey of the children and adolescents target group based on the STROBE statement

The participation in the scientific investigation and the information are voluntary for the paediatricians as well as the C&A and their parents. The primary data is collected by the evaluator’s staff. The inclusion of the subjects is carried out after complete clarification and presentation of a written declaration of consent. Participants can revoke their consent at any time. The evaluation of the data is pseudonymised.

The primary data collected and the secondary data used are stored in pseudonymised form on a secure, encrypted network drive at the Hannover Medical School (MHH) and the access rights are limited to the project staff. A transmission or passing on of data to third parties is excluded. No information is transmitted to third parties that could allow conclusions to be drawn about individual persons. All data will be stored on a secure, encrypted hard disk after completion of the study and deleted after 10 years at the earliest (in accordance with the recommendations on safeguarding good scientific practice).

### Statistical analysis

#### Qualitative analyses

The qualitative interviews are recorded with dictation machines and then transcribed. The analysis of the transcripts follows the procedure of inductive category development as well as the qualitative, summarizing content analysis according to Mayring [24]. The data is evaluated with the MAXQDA software.

#### Quantitative analyses

The data evaluations are initially performed descriptively. The hypotheses developed are also tested for inferential statistics. In order to ensure comparability between participating and non-participating insured persons, a CG is formed for the IG on the basis of the routine data using the characteristics gender, age and comparable region. Participants from both groups are brought together with PS matching at the individual level. The analyses of the primary data take into account in particular covariates for which it was not possible to match at the secondary data level, such as socio-economic status and migration background. The influence of the selective contract is checked using ANCOVA. The analyses are carried out with the software programs SAS, SPSS and Microsoft Excel.

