**Discussion:**

Around 560 pediatricians and 63,000 C&A currently participate in the AOK Nordost care program. The project provides information to what extent secondary preventive measures can lead to the early detection of diseases and on the associated cost-effectiveness. Furthermore, potentials and barriers of the program implementation are identified. The results of the evaluation study are expected not only to contribute to the further development of the care program, but also to derive recommendations for action.

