The selective contract “Pediatric-centred integrated care AOK-Junior (AOK-Junior)” completes the legally defined medical care for insured persons up to the age of 18 in cooperation with qualified paediatricians. AOK-Junior focuses on health protection, early detection and prevention with the aim of maintaining C&A’ health and detecting and preventing diseases at an early stage. By participating in AOK-Junior, quality, service and coordination of treatment and prevention for C&A should be improved compared to standard care.

The AOK Nordost is responsible for preventive measures in addition to program development. The target group of this contract is therefore the entire population of children and young people insured with AOK Nordost (approx. 250,000) and their parents. The number of participating insured persons is approximately 65,000 C&A (August 2019). Thus, more than one fifth of the C&A insured under the AOK Northeast insurance participate in AOK-Junior.

Responsible for the implementation of the defined services is the BVKJ-Service GmbH. BVKJ-Service GmbH represents the interests of approx. 560 paediatricians (August 2019) participating in AOK-Junior.

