### Medical services of the selective contract

At the centre of the health care provision for C&A within the framework of AOK-Junior is the paediatrician, who coordinates the general medical-paediatric and specialist care. AOK-Junior comprises the following modules:
The performance module includes additional early detection examinations: The focus of the **U10** (age 7–8) is, among other things, the recognition of motor development disorders as well as developmental and behavioural disorders. The **U11** (age 9–10) includes, among other things, the recognition of school performance disorders, socialisation disorders, behaviour harmful to health as well as tooth, mouth and jaw anomalies. The focus of **J2** (age 16–17) is the recognition/treatment of puberty and sexuality disorders, posture disorders, goitre formation as well as diabetes prevention and counselling in questions of behaviour, socialisation, family and sexuality.Performance module **Allergic Rhinitis**: The module promotes specific immunotherapy (SIT) for AOK-Junior participants with allergic rhinitis. By using a reminder system, the high current dropout rate is intended to be reduced and the rate of successfully completed hyposensitizations increased.Performance module **Ophthalmologic Early Screening Examination**. The module is intended to promote the early detection of eye diseases, visual defects and strabismus in children between the ages of 32 and 42 months. An individual consultation should avoid eye damaging influences and behaviours.**Lung Check** performance module. The aim of the Lung Check module is to prevent a chronic respiratory disease, to provide information about possible therapies and to positively influence the course of the disease. The preventive care benefit can be claimed by 6- to 7-year-olds under certain conditions and includes an outpatient pneumological examination as well as a health education consultation.**Skin Check** performance module. The skin check includes additional measures for the early detection and treatment of chronic skin diseases. Individual consultations are intended to help avoid skin-damaging influences and behaviours. The first skin check is aimed at 2 to 5-year-olds, the second at 13 to 17-year-olds.Performance module **Dental Health**. AOK-Junior participants receive a subsidy if the premolars have to be sealed. In addition, professional dental cleaning for AOK-Junior participants with ongoing orthodontic treatment can be subsidized.Performance module **Target Agreement on Overweight**. In order to reduce the morbidity and mortality risk of overweight or obese AOK-Junior participants in adulthood, a target agreement for weight reduction is concluded with either the participants or one parent. It is also essential to provide information on overweight and obesity, their serious health consequences and weight reduction options. If the goals are achieved, there is a bonus gift for the AOK-Junior participants. The measure is intended to bring about a change in dietary and movement habits.

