**Fig. 2 Fig2:**
[figure not shown]
Flowchart for the primary survey among the target group of paediatricians based on the STROBE Statement

At the level of the C&A, all patients who have used the services are included in the IG as part of the secondary data analyses. Using PS matching, a suitable CG is drawn from the secondary data in a ratio of 1:1. The collection of primary data takes place in a sub-sample, whose case number was calculated on the basis of the primary outcome parameter of the health-related quality of life. A 2 × 3-factorial design is used to compare the intervention with standard care (IG/CG) (factor 1), taking into account multiple factors, e.g. the region (factor 2). To demonstrate expected small effects at the significance level of α ≤ 0.05 and a power of 80%, a net sample of *n* = 1096 (*n* = 548 per group) is required for analysis. With a conservatively expected response rate of 40%, a sample of *n* = 2740 is invited to participate. The case number planning and the analysis methods are selected in order to adjust for covariates (e.g. gender). The expected course of the study for the target group is shown in Fig. 3.

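### The stated analysis makes no allowance for clustering of children by paediatrician, so routine-data standard errors would be understated if the two groups attend largely different practices

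*Protocol article*

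**What the plan says.** The Quantitative analyses section (Statistical analysis) forms the control group from routine data "using the characteristics gender, age and comparable region". It then states: "Participants from both groups are brought together with PS matching at the individual level". The inferential method is given in one sentence: "The influence of the selective contract is checked using ANCOVA". The sample size section adds the ratio: "Using PS matching, a suitable CG is drawn from the secondary data in a ratio of 1:1".

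On delivery, the Intervention section reports: "BVKJ-Service GmbH represents the interests of approx. 560 paediatricians (August 2019) participating in AOK-Junior". The abstract says: "Around 560 pediatricians and 63,000 C&A currently participate in the AOK Nordost care program"; the Intervention section puts the enrolled children at about 65,000. Under Medical services of the selective contract, at the centre of care "is the paediatrician, who coordinates the general medical-paediatric and specialist care".

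The article mentions no practice effect, intraclass correlation, multilevel model, GEE or cluster-robust error. It names no variance method for time of detection, incidence or cost.

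**The concern.** The main outcomes are when a chronic disease is detected and how often (H1, H2), read from routine data. Cost per detected case builds on the same detections. The paediatrician acts as gatekeeper and coordinates specialist care, so children of one practice plausibly share habits of examination, coding and referral. Their outcomes are then correlated.

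Matching on sex, age and region does not balance practices, and ANCOVA in its standard form assumes independent errors. If the groups come from different sets of practices, chance differences between practices enter the group contrast without entering its standard error. Intervals for detection and cost would be too narrow, and a difference between practices could be reported as a programme effect. The Discussion offers the results as a basis for future decisions and investment in prevention.

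**Working it through.** **The plan's own figure.** The only powered analysis is the quality-of-life survey: 1096 net, 548 per group, 2740 invited. The article gives no numerical effect size. Taking small as Cohen's f = 0.10 (assumed), with alpha 0.05 and power 80%, a noncentral-F calculation gives N = 1095 at 3 numerator degrees of freedom, or 1096 when split evenly. Other choices miss: 787 at 1 df, 967 at 2, 1199 at 4 and 1289 at 5. Then 1096 / 0.40 = 2740. The figure is thus reached by an individual-level calculation with no room for a design effect.

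**Cluster size.** 63,000 / 560 = 112.5, or 65,000 / 560 = 116.1 enrolled children per paediatrician.

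**No shared practices.** Design effect DEFF = 1 + (m − 1) × ICC. The standard error is understated by √DEFF. The true size of a nominal 5% two-sided test is 2 × [1 − Φ(1.96 / √DEFF)]. The documents give no ICC, so a range is assumed.

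| ICC (assumed) | DEFF, m = 112.5 | √DEFF | Type I | DEFF, m = 116.1 | √DEFF | Type I |
|---|---|---|---|---|---|---|
| 0.001 | 1.11 | 1.05 | 6.3% | 1.12 | 1.06 | 6.3% |
| 0.01 | 2.12 | 1.45 | 17.8% | 2.15 | 1.47 | 18.1% |
| 0.02 | 3.23 | 1.80 | 27.5% | 3.30 | 1.82 | 28.1% |
| 0.05 | 6.58 | 2.56 | 44.5% | 6.75 | 2.60 | 45.1% |

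**Half the controls in participating practices.** Suppose the IG fills k practices with m children each. Half the controls are spread evenly over those k practices and half over k others. Each practice then carries a net weight of 1/(2k) in the group difference. The squared weights sum to 2k × 1/(4k²) = 1/(2k). Relative to the independent-data variance, 2/(km), the ratio is (1 − ICC) + ICC × m × 0.25. With m = 112.5:
- ICC 0.01: 0.99 + 0.28 = 1.27, type I about 8%
- ICC 0.02: 0.98 + 0.56 = 1.54, type I about 11%
- ICC 0.05: 0.95 + 1.41 = 2.36, type I about 20%

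**All practices shared equally.** The practice terms cancel and the ratio is 1 − ICC: 0.99 at ICC 0.01 and 0.95 at 0.05. Standard errors that ignore practice are then slightly too large.

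**Survey.** With 548 IG children drawn at random over 560 practices, the size-weighted cluster size is 1 + 547/560 = 1.98. DEFF is 1.01 at ICC 0.01 and 1.05 at 0.05, and the net sample would rise from 1096 to about 1107 to 1150.

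**The case against.** The strongest objection is that the article never says children are treated as independent. The matching sentence describes how controls are chosen, and individual matching can be combined with clustered errors. An analysis plan that is not shown may supply them. The ANCOVA sentence directly follows one about the primary data, so it may be meant mainly for the survey, where clustering is minor. All of this stands, and it is why the point is conditional. What remains is that the article states the unit of matching and one model, and an analyst who applied them to the routine data would assume independence.

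The direction is also open. Controls are defined only as AOK-insured children outside the programme and may attend participating paediatricians. This stands too, but full sharing is unlikely. The paediatrician survey contacts about 1000 doctors, of whom 564 participate. Roughly 185,000 of the 250,000 insured children are not enrolled, and nothing ties controls to participating practices. The Background adds that older children often move to general practitioners. Full sharing also protects only if the programme effect is constant across practices.

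The size can be challenged as well. The IG is limited to children who used services, and each module has its own population. For the eye module (ages 32 to 42 months), even ages and full uptake at one point in time give about 116 × 11/216 ≈ 6 children per paediatrician. DEFF is then 1.05 to 1.25 and type I error about 6% to 8% at ICC 0.01 to 0.05. Several years of data would raise this and low uptake would lower it. If controls were not clustered at all, the ratio at ICC 0.01 would be about (2.15 + 1)/2 ≈ 1.6. A reader might infer that disease-specific analyses suffer most; smaller clusters point the other way.

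**Conclusion.** The concern holds in conditional form. The stated analysis contains no allowance for practice, and care is organised through a limited number of doctors. If the routine-data comparisons of detection and cost follow it, and the groups use largely different practices, the all-children standard errors are too small by a factor of about 1.05 at ICC 0.001, 1.5 at 0.01 and 2.6 at 0.05. Substantial but incomplete sharing still leaves type I error at about 8% to 20% for ICC 0.01 to 0.05.

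These figures rest on assumed ICCs, equal cluster sizes, similar clustering in both groups and all enrolled children being analysed. A reader might infer that the plan definitely produces undersized standard errors, or that paediatricians make all the diagnoses. The documents support neither: no variance method is given for these outcomes, practice overlap is not described, and some modules involve dental or specialist lung care. The change is nevertheless worth making, because it corrects the standard error in whichever direction the overlap pushes it.

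**What to change.** State that every routine-data model for detection (H1, H2) and cost uses standard errors clustered on the child's main treating practice at the index date, or a random intercept for that practice. If cost intervals are bootstrapped (the article mentions no bootstrap), resample practices rather than children. Report how many practices contribute to each group and how many contribute to both.

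The change needs no new data collection and no change to the matching. It does assume that the treating practice can be identified in the billing data. It also needs an attribution rule, fixed in advance, for children who see several doctors or have moved to a general practitioner. Intervals will usually be wider. The survey sample size need not change on this account.

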#### Evaluation of the structural quality

The evaluation of the structural quality is carried out on the basis of cross-sectional analyses of the available routine data. Reference data are used to evaluate the degree of achievement. In addition, primary data on structural features are collected as part of the quantitative cross-sectional survey of paediatricians. In this context, the cross-sectional design is well suited to examining the absolute and relative frequency of structural features between participating and non-participating physicians or insured persons. The structural characteristics of the physicians include, for example, region, group of specialists, size of practice, practice kind (single practice, joint practice or practice communities), number of patients treated per quarter, age and sex. Among the structural characteristics of insured persons are e.g. age, sex, nationality, income, education and occupational status (of parents) and chronic diseases (diabetes mellitus, ADHD, asthma, allergy and obesity).

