### Measurements

Within the scope of the project, the instruments for primary surveys shown in Table 1 with the parameters mentioned will be developed for the target groups. In addition, the performance and accounting data of AOK Nordost will be included in the analyses.

**Table 1 Tab1:** Survey instruments and parameters

Target group	Instrument	Parameter
Paediatricians	Structured interview guide for the focus group survey	Barriers / hindering factors, potentials / promoting factors, satisfaction
	Partially standardised questionnaire	Participation, abortion reasons, practice size/form, specialist group, age (year of birth), gender, work experience, region, working time per week, number of patients treated per quarter, proportion of private patients, satisfaction, incentives, barriers / obstructive factors, potentials / promoting factors
Children and adolescents	Structured interview guide for the focus group survey	Barriers / hindering factors, potentials / promoting factors, satisfaction, expected benefit, effort
	Partially standardised questionnaire	Age (year of birth), gender, sociodemography (income, education, migration, occupational status), region, satisfaction, barriers / hindering factors, potentials / promoting factors, expected benefit / incentives, effort, utilization of U-examinations (U8, U9), health-related quality of life (KIDSCREEN 27), health behavior, body size and weight

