### Study population

The underlying study population consists primarily of an IG and a CG at paediatricians as well as C&A level. The AOK-Junior selective contract is implemented in entire catchment area of the AOK Nordost. At the level of paediatricians, all participating physicians are included in the quantitative survey. The CG includes doctors who are also organised in the BVKJ but do not participate in the selective contract AOK-Junior. For the inclusion of the CG, it is considered that these are active in catchment areas that are as comparable as possible. A sub-sample will be taken for the qualitative surveys. Thereby, an adequate representation of the range of catchment areas of established paediatricians is taken into consideration.

At the level of the insured, the study population is drawn on the basis of routine data. The participants of the IG are C&A from birth up to and including the age of 17. Thus for each module its own population is needed. The exception is the target agreement on overweight. In the CG are C&A who are also insured with the AOK, but who do not participate in the AOK-Junior prevention programme. In order to ensure comparability between participating and non-participating insured persons, a CG is formed for the IG on the basis of routine data using the characteristics of sex, age and comparable region by means of PS matching.

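### The main routine-data comparisons (H1–H5) are matched only on sex, age and region; recognised social confounders are adjusted for only in the survey, and the article is inconsistent about where those items come from

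*Protocol article*

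**What the plan says.** All references are to the protocol article.

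- **Evaluation of the structural quality.** The evaluation is "carried out on the basis of cross-sectional analyses of the available routine data". One further source is named: "primary data on structural features are collected as part of the quantitative cross-sectional survey of paediatricians". The aim is to compare the "absolute and relative frequency of structural features between participating and non-participating physicians or insured persons". The examples given for insured persons include "age, sex, nationality, income, education and occupational status (of parents) and chronic diseases".
- **Study population.** The control group is formed from routine data "using the characteristics of sex, age and comparable region by means of PS matching". The Quantitative analyses section repeats the same three variables.
- **Quantitative analyses.** The primary-data analyses are to allow for "covariates for which it was not possible to match at the secondary data level, such as socio-economic status and migration background". No such step is described for the routine-data analyses.
- **Evaluation of outcome quality.** Time of detection (H1) and incidence (H2) come from the routine-data cohort. The health economic analysis builds on those results. The Abstract likewise bases effectiveness on secondary data.
- **Measurements, Table 1.** The questionnaire for children and adolescents records "sociodemography (income, education, migration, occupational status"). Nationality is not among its listed items.

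**The concern.** There are two linked problems.

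**Source.** Read as written, the structural-quality section places parental social status and nationality in a comparison fed by routine data and a physician survey. The analysis section says socio-economic status and migration background could not be matched in routine data. A reader cannot tell whether the insurer holds some of these items, in which case they belong in the propensity score, or does not, in which case the structural comparison needs another named source.

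**Confounding.** The article accepts that socio-economic status and migration background need adjustment, but applies it only to the survey, which is sized on health-related quality of life. The main question, earlier detection of disease, is answered from routine data without it. Enrolment in a voluntary screening programme and the recording of a diagnosis can both plausibly depend on social status and migration. A difference between the groups on H1–H5 could then partly reflect who enrols. The survey is drawn from participants and non-participants in the same insurer's data and will show how they differ on most of these variables, yet no use of it for the main results is described.

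**Working it through.** The plan gives no figure to reproduce, so the check sets the sections side by side and then illustrates the scale.

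**1. Source of each item**

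| Item | Listed under structural quality | In matching set | In questionnaire (Table 1) |
|---|---|---|---|
| Age, sex | yes | yes | yes |
| Region | for physicians | yes | yes |
| Parental income, education, occupation | yes | no | yes |
| Nationality | yes | no | no (migration only) |
| Migration background | no (nationality only) | no | yes |

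The questionnaire can supply the parental items, but the structural-quality section does not name it. For nationality no survey source is listed. The article does not say whether the insurer holds it.

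**2. Where adjustment applies**

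H1 and H2 are explicitly routine-data outcomes. H4 and H5 follow from insurer costs and those outcomes. H3 (earlier therapy) is an effectiveness hypothesis, which the Abstract assigns to secondary data, and Table 1 has no therapy item. All five therefore fall on the side with no described adjustment for social status or migration.

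**3. Illustrative bias**

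Take one binary unmatched confounder (low social status) with share p1 in the intervention group and p0 in the control group, and rate ratio RR for a recorded diagnosis. With no programme effect the observed intervention/control ratio is

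B = [1 + p1(RR − 1)] / [1 + p0(RR − 1)].

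All shares and rate ratios here are assumptions.

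| p1 / p0 | RR | B |
|---|---|---|
| 0.30 / 0.40 | 1.2 | 1.06/1.08 = 0.981 |
| 0.30 / 0.40 | 1.5 | 1.15/1.20 = 0.958 |
| 0.30 / 0.40 | 2.0 | 1.30/1.40 = 0.929 |
| 0.20 / 0.40 | 2.0 | 1.20/1.40 = 0.857 |
| 0.20 / 0.40 | 0.5 | 0.90/0.80 = 1.125 |
| 0.30 / 0.50 | 0.5 | 0.85/0.75 = 1.133 |

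The first three rows give a shift of about 2–7%. The wider range runs from about 0.86 to 1.13, on both sides of 1.

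**4. Chance of false significance**

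Assume 5% incidence. For n pairs, treating the groups as independent, SE of the log ratio = √(2 × 0.95 / (0.05 n)). The rejection probability at two-sided 5% follows from a normal variable with mean ln(B)/SE and variance 1. For 0.30 versus 0.40:

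| Pairs | SE | RR 1.2 | RR 1.5 | RR 2.0 |
|---|---|---|---|---|
| 65,000 (all enrollees) | 0.0242 | 12% | 42% | 87% |
| 10,000 (assumed) | 0.0616 | 6% | 11% | 22% |
| 5,000 (assumed) | 0.0872 | 5–6% | 8% | 14% |

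The 65,000 is the enrolment figure under Intervention and is an upper bound. The sample size section limits the intervention group to those who used services, and the Study population section calls for a separate population per module.

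**5. Precision of the survey as an input**

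With 548 per group, the SE of a 30% versus 40% difference is √(0.30 × 0.70/548 + 0.40 × 0.60/548) = 0.029, so 10 percentage points is known to about ±5.6 points before any non-response bias.

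**The case against.** **The sections can be read as consistent.** The structural-quality list is introduced as examples and assigns no source item by item. Table 1 collects the parental items from both groups, and the analysis section treats social status and migration as survey variables. This largely stands. A reader might infer that the structural comparison has no source at all; for the parental items Table 1 shows otherwise. What remains is that the section names the physician survey, omits the questionnaire that is needed, and lists nationality, which the questionnaire does not.

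**Held confounders are not shown to be left out.** A reader might infer that the insurer holds parental income or education and ignores them. Nothing in the article shows this, and the analysis section points the other way. Equally, being impossible to match is not the same as not being held, and nationality is not the same variable as migration background. The article does not settle the matter.

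**The limit is disclosed, and a sensitivity analysis may sit in the full study plan.** The matching limit is indeed stated openly. But the article itself fixes the matching set twice and says where the adjustment applies. The point rests on what is written there.

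**The size can be overstated.** This stands. The 12/42/87% rates require every enrollee to be a matched pair; at smaller module populations they fall sharply. The scenarios with RR above 1 push the ratio below 1, which for H2 would mask a benefit, not create one. With RR below 1 the bias goes the other way.

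**The survey cannot correct the results by itself.** This also stands. It gives group distributions, not the association of social status with diagnosis, therapy or cost; Table 1 has no such outcomes and no linkage to routine data is described. Its respondents may also differ from the module populations.

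**Conclusion.** The point holds as two findings: a source inconsistency that needs reconciling, and residual confounding of the routine-data results for H1–H5 by variables that the article itself regards as needing adjustment.

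The direction is unknown. Under assumed shares of 30% versus 40% and rate ratios of 1.2 to 2.0 the incidence ratio shifts by about 2–7%; under the wider assumptions the shift reaches about 14%. These figures rest wholly on assumed inputs, because the documents give none, and they illustrate a ratio such as that in H2; detection time and costs would need their own inputs. The bias does not depend on sample size, but the chance that it produces a significant result does, so no single false-significance rate can be attached to the plan. It should be addressed, at modest cost. It does not invalidate the design.

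**What to change.** 1. Reconcile the structural-quality and Quantitative analyses sections by stating which of nationality and parental income, education and occupation the insurer's data hold, and in what form.
2. Add any held item, for example nationality if available, to the propensity score alongside sex, age and region.
3. Name the children-and-adolescents questionnaire as the source for the remaining insured-person characteristics. If nationality is neither held nor asked, replace it with migration background or add it to the questionnaire.
4. Report, beside the unadjusted results for all of H1–H5, a quantitative bias analysis that uses the survey's distributions in the two groups and a pre-stated range of covariate–outcome associations on both sides of the null. Use propensity-score calibration only if survey answers can be linked to routine data and consent allows it.

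**Cost.** A wording change, possibly extra matching variables, and a limited analysis on data already planned. The adjusted results carry the survey's sampling error, its expected 40% response, a possible mismatch with the module populations, and the assumed associations. They should be presented as a sensitivity analysis and not replace the main estimates.
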